### Baseline analyses

To assess external generalisability, demographic and clinical characteristics of patient participants invited to participate in the study at baseline will be compared with participants who are subsequently randomised and participants who are screened but not randomised. The specific criteria by which participants are excluded from randomisation will be tabulated. Baseline comparability will be assessed using descriptive statistics only.

### Number of Participants

#### Part 1

A sample size of 50 MHNs will be sought (25 in the HIP and 25 in the TAU group), with 5 patients each resulting in an overall sample size of 250 patients (125 in the HIP and 125 in the TAU group). Based on a standard deviation of about 12 points as found in MOS patients (adults in various settings with SMI in the US), a difference in means between intervention and TAU of 6 points in the SF36v2 PCS subscale is equivalent to a medium effect size. The proposed sample size gives a power of 86% to detect this if an intraclass correlation of 0.1 is assumed and nearly 80% if an intraclass correlation of 0.2 is assumed using a 2-sided significance level of 0.05 and allowing for an estimated 20% attrition rate i.e. 1 patient per nurse.

All MHNs in the HIP and TAU groups will be invited to participate in the online PHASe adapted at baseline and one year. Response rates will be reported. All patients remaining the HIP Group at one year will provide data for evaluation of any change in their QRISK^®^2 Scores. Retention rates will be reported.

#### Part 2

The patient records of the 36 randomly selected patients from the HIP Programme Group will be audited using the HIP Audit Form. We will purposefully recruit from the HIP Group (on completion of Part 1) 10 patients to participate in the Patient Semi-structured Interviews, 10 nurses to participate in a Focus Group (per Trust study site) 5 psychiatrists and 5 GPs to participate in the telephone interviews. (30 in total). The aim of this element of the project is to elicit general feedback that will help in refining and further developing the HIP. The qualitative literature indicates that this number of data collection interviews per homogenous professional or patient group should allow us to reach saturation of themes [46].

### Feasibility of target sample size

Localities in the two NHS sites provide services via community mental health, assertive outreach and recovery teams. Across the two NHS Trusts there are a total of 16 localities and 33 teams. We will invite every band 5-7 MHN in these teams to participate and once recruited, screen every patient on their caseload for the inclusion criteria before inviting randomly selected patients to take part as a patient subject in the randomised trial. To make this achievable we will work closely with Clinical Team Leaders. Our planned recruitment rate is 25 patients per month (excluding August and December).

### Efficacy analysis

Efficacy of the intervention will be assessed by comparing the patient outcomes at 52 weeks between the two groups allowing for the clustering effect of the nurse. Further, adjusted estimates will be obtained by identifying baseline variables that differ between the two groups, which are related to the outcome and incorporating these into the analyses.

### Inclusion in Analysis

An intention to treat (ITT) analysis will be performed. The ITT analysis set will comprise all patients who were randomised to a group at baseline (HIP Programme or TAU group), irrespective of any change to the other group over the course of the trial. This is the main analysis and will be used for evaluation of all endpoints. However, we acknowledge there may be attrition due to nurses leaving teams and where patients may be unavoidably switched to a nurse participant caseload in a group other than the one they were randomised to at baseline or to a MHN not in the study. To enable an evaluation of the effects of this on the primary outcome we will undertake and report a secondary per protocol [PP] analysis. HIP and non-HIP patients will be included in groups on an intention to treat basis. The primary analysis will include non-missing data only. However, where there is attrition at follow up the baseline characteristics of missing and non-missing values will be compared. Further, we will perform sensitivity analyses by (i) assuming zero change in scores and (ii) employing current multiple imputation techniques.

A per protocol analysis will also be performed. Per protocol will be defined as the participant remaining in the same arm of the study as at randomisation.

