**Methods/Design:**

A single blind parallel group cluster randomised controlled trial with secondary economic analysis and process observation. Unit of randomisation: mental health nurses [MHNs] working in adult community mental health teams across two NHS Trusts. Subjects: Patients over 18 years with a diagnosis of schizophrenia, schizoaffective or bipolar disorder on the caseload of participating MHNs. Primary objective: To determine the effects of the HIP programme on patients' physical wellbeing assessed by the physical component score of the Medical Outcome Study (MOS) 36 Item Short Form Health Survey version 2 [SF-36v2]. Secondary objectives: To determine the effects of the HIP programme on: cost effectiveness, mental wellbeing, cardiovascular risk, physical health care attitudes and knowledge of MHNs and to determine the acceptability of the HIP Programme in the NHS. Consented nurses (and patients) will be randomised to receive the HIP Programme or treatment as usual. Outcomes will be measured at baseline and 12 months with a process observation after 12 months to include evaluation of patients' and professionals' experience and observation of any effect on care plans and primary-secondary care interface communication. Outcomes will be analysed on an intention-to-treat (ITT) basis.

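### The primary PCS comparison carries an all-randomised ITT label but uses observed 52-week scores only, without conditioning on baseline PCS, so arm-dependent dropout can bias it avoidably

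*Protocol article*

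**What the plan says.** All references are to the protocol article.

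- **Population.** Inclusion in Analysis: "The ITT analysis set will comprise all patients who were randomised to a group at baseline". Of the analysis on that set it says "This is the main analysis and will be used for evaluation of all endpoints". The abstract (Methods/Design) says without qualification: "Outcomes will be analysed on an intention-to-treat (ITT) basis".
- **Data used.** Later in the same section: "The primary analysis will include non-missing data only". It then plans a baseline comparison of patients with and without follow-up data, and two sensitivity analyses: zero change in scores, and multiple imputation.
- **Model.** Description of Statistical Methods compares arms by regression with a random term for nurse. The baseline value of the outcome enters only in further adjusted estimates. Efficacy analysis has the same order: the 52-week comparison allowing for nurse clustering first, adjusted estimates after it.
- **Timing.** Baseline and follow up assessments gives two time points, baseline and 52 weeks.
- **Attrition.** Number of Participants sets the sample "with 5 patients each resulting in an overall sample size of 250 patients (125 in the HIP and 125 in the TAU group"), and computes power "allowing for an estimated 20% attrition rate i.e. 1 patient per nurse".

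**The concern.** Two things combine. First, the label does not match the analysis. The set called the main analysis holds every randomised patient, but with one follow-up visit and no baseline term, a patient without a 52-week PCS contributes nothing to the leading estimate.

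Second, that estimate makes no use of the one measurement every patient should have and that is likely to predict the outcome best: baseline PCS. If patients in poorer physical health leave one arm more readily than the other, the completers differ between arms at baseline, and the unadjusted 52-week difference carries that imbalance.

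Arm-dependent dropout is plausible here, though not established. Potential Bias accepts that self-reports may depend on the assigned arm, so patients are taken to know it, and only HIP patients go through a 27-item profile that flags unhealthy items. At stake are the size and error rate of the headline result, and whether readers are told correctly what population it describes.

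**Working it through.** **1. Inputs from the protocol article (Number of Participants).** 25 nurses per arm, 5 patients each; "Based on a standard deviation of about 12 points"; "a difference in means between intervention and TAU of 6 points in the SF36v2 PCS subscale"; ICC 0.1 or 0.2; two-sided 5% level; 20% attrition.

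**2. Patients left out.** 0.20 × 250 = 50, leaving 200 (100 per arm, 4 per nurse).

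**3. The plan's own power.** Effective n per arm = 100 / (1 + 3 × ICC).

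| ICC | Effective n per arm | SE = 12 × √(2/n) | Power, normal | Power, t with 48 df | Stated |
|---|---|---|---|---|---|
| 0.1 | 76.9 | 1.93 | 87.3% | 86.0% | 86% |
| 0.2 | 62.5 | 2.15 | 79.8% | 78.2% | nearly 80% |

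The stated power reproduces, and it already rests on the 200 observed patients. The issue is bias and labelling, not sample size.

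**4. Bias of the unadjusted completers' difference.** These inputs are assumptions and are not in the documents: baseline-to-52-week PCS correlation ρ of 0.5 to 0.7; logistic dropout with slope b per SD of baseline PCS; 20% lost in each arm; true effect 0.

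Let Z be standardised baseline PCS and p(Z) = 1 / (1 + exp(−(a + bZ))), with a set so that the mean of p is 0.20. The completers' mean baseline is shifted by

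s(b) = E[Z × (1 − p(Z))] / 0.80.

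Numerical integration gives s(0) = 0, s(−0.5) = 0.096 (a = −1.459), s(+0.5) = −0.096 and s(−1) = 0.173 (a = −1.650). Then

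bias = ρ × 12 × (s for HIP − s for TAU).

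| Slopes (HIP, TAU) | Difference in s | Bias, ρ = 0.5 | Bias, ρ = 0.7 | Simulated range |
|---|---|---|---|---|
| (0, 0) | 0 | 0 | 0 | about 0 |
| (−1, −1) | 0 | 0 | 0 | about 0 |
| (−0.5, 0) | 0.096 | 0.58 | 0.81 | 0.57 to 0.86 |
| (−1, 0) | 0.173 | 1.04 | 1.46 | 0.96 to 1.45 |
| (−0.5, +0.5) | 0.192 | 1.15 | 1.62 | 1.08 to 1.60 |

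The simulations used 50 nurses × 5 patients, ICC 0.1 and 2,000 to 4,000 trials per scenario. With these signs the bias favours HIP; reversing them reverses it.

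**5. Size.** 0.6 / 6 = 10% and 1.6 / 6 = 27% of the target. Against the SE of 1.93 that is 0.6 / 1.93 = 0.3 to 1.6 / 1.93 = 0.8. Simulated two-sided type I error was 4 to 5% without differential dropout and 5 to 12% with it.

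**6. What removes it.** In the same scenarios:

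| Analysis | Largest bias | SE |
|---|---|---|
| Observed data, unadjusted | about 1.6 | about 1.9 |
| Observed data, adjusted for baseline PCS | within about 0.1 of zero | 1.4 to 1.7 |
| Multiple imputation, then unadjusted comparison | within about 0.1 of zero | 1.8 to 2.0 |

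The first two rows use the same patients. Here the bias comes from not conditioning on baseline PCS, not from using observed outcomes as such.

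**The case against.** The strongest reply is that the section is coherent if read generously: the ITT definition says which arm a patient counts in, and the sentence on non-missing data says how absent outcomes are handled. The power calculation on about 200 patients fits that reading. Missing data are also not neglected, since a baseline comparison, a zero-change analysis and multiple imputation are all planned. Finally, every dropout slope above is hypothetical, and the cause of attrition the plan names, nurses leaving teams, is not obviously tied to patients' PCS.

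Much of this stands. A reader might infer any of the following, and the document supports none of them:

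- *Either result could be presented as the main one if they disagree.* The section ranks non-missing data as primary and imputation as sensitivity.
- *Missing data go unexamined.* They are examined, but only outside the primary analysis.
- *The trial loses power it did not allow for.* The 20% loss is in the calculation.
- *Imputation must become primary.* The adjusted observed-data model removes the same bias with a smaller SE.

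What the reply does not remove is narrower. The set named as the main analysis is every randomised patient, and the leading estimate does not meet that description under any reading. That estimate also omits an adjustment that is already planned and removes this bias. The per protocol analysis that Potential Bias offers as the check on attrition does not help, because it is defined by staying in the same arm and recovers no missing outcome.

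**Conclusion.** The point holds in limited form. The leading primary estimate is an unadjusted comparison of about 200 of 250 patients under an all-randomised ITT label, and it is open to avoidable bias of about 0.6 to 1.6 PCS points (10 to 27% of the target) if dropout depends on baseline PCS differently by arm.

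That range rests on assumed slopes of 0.5 to 1 per SD, correlations of 0.5 to 0.7, and 20% loss in each arm. The bias is possible, not certain: it is nil if dropout is unrelated to baseline PCS or related equally in both arms. The adjusted model and the imputation both assume data missing at random given baseline. If dropout depends on the unobserved 52-week score beyond what baseline explains, neither is guaranteed to remove the bias.

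**What to change.** 1. In Description of Statistical Methods and Efficacy analysis, make the already planned model with baseline PCS and the nurse random term the primary analysis, using all observed 52-week scores by randomised arm. State that it assumes data missing at random given baseline.
2. In Inclusion in Analysis and the abstract, describe it as an available-case analysis by randomised arm, not as ITT on all randomised patients.
3. Keep multiple imputation, with arm, nurse and baseline PCS in the imputation model, as the analysis that includes every randomised patient. Report the unadjusted completers' comparison as secondary only.

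Making the imputation primary is an acceptable alternative. It removes the same bias but is less precise (SE 1.8 to 2.0 against 1.4 to 1.7) and ties the headline result to an imputation model that must be pre-specified and respect nurse clusters.

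The cost is a few sentences of wording and a reordering of analyses already planned. It needs no new data and no more patients.

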## Analysis

### Description of Statistical Methods

The analysis and reporting of the trial will be undertaken in accordance with Consolidated Standards of Reporting Trials [CONSORT] [44,45]. Standard methods will be used to provide tabular and graphical summaries as appropriate for continuous and categorical variables. Primary and secondary outcomes will be compared between intervention and control groups using linear or logistic regression as appropriate including a random term to allow for nurse clusters. Further adjusted estimates will be calculated by including the baseline value of the outcome in these models. Where between group differences are observed in demographics or patient characteristics at baseline, terms representing these variables will also be included to obtain adjusted estimates of the intervention effect. The characteristics of the MHNs will be compared between groups. If differences occur these may be incorporated into a multilevel model structure. The latest available versions of the Statistical Package for the Social Sciences [SPSS] and Stata will be used for the analysis. It is not our intention to conduct any subgroup analyses.

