### Potential Bias

The subjective nature of the self-report instruments, used for assessment, is accepted and every effort will be made to minimise potential bias which may occur due to this dynamic. In particular, patients may over or under report their health status depending on the trial arm to which they have been assigned. We acknowledge there may be attrition so to enable an evaluation of the effects of this on the primary outcome we will undertake a secondary per protocol[PP] analysis to compare with the ITT.

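### The zero-change sensitivity analysis tests one fixed assumption about lost patients, is not reliably conservative, and leaves differences between lost HIP and lost TAU patients untested.

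*Protocol article*

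**What the plan says.** In the protocol article, Inclusion in Analysis defines the main analysis as intention to treat and then adds: "The primary analysis will include non-missing data only". Attrition is addressed there in two further ways. First, "where there is attrition at follow up the baseline characteristics of missing and non-missing values will be compared". Second: "Further, we will perform sensitivity analyses by (i) assuming zero change in scores and (ii) employing current multiple imputation techniques".

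The same section expects loss: "we acknowledge there may be attrition due to nurses leaving teams". Number of Participants puts a size on it, "allowing for an estimated 20% attrition rate i.e. 1 patient per nurse", which is about 50 of 250 patients. Baseline and follow up assessments lists only two time points, baseline and 52 weeks.

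Efficacy analysis describes "comparing the patient outcomes at 52 weeks between the two groups allowing for the clustering effect of the nurse". Description of Statistical Methods adds: "Further adjusted estimates will be calculated by including the baseline value of the outcome in these models". Potential Bias accepts that "patients may over or under report their health status depending on the trial arm to which they have been assigned", and offers the per protocol analysis as a way to judge the effect of attrition.

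**The concern.** With no visit between baseline and 52 weeks, zero change means baseline carried forward for a full year. It is a single imputation with one value per lost patient, under the same assumption in both arms and with no range around it.

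The main analysis omits patients without a 52-week score, so the sensitivity analyses carry most of the protection against attrition bias. The per protocol analysis adds little here: it is defined by staying in the randomised arm, which concerns switching and recovers no missing outcome.

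If the zero-change result agrees with the main result, readers will take the finding as robust to attrition. That inference is sound only if the rule leans in a known direction, or if it probes the assumption most open to doubt, namely that lost patients in the two arms fared alike given what was observed.

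**Working it through.** **Inputs from the protocol article.** 25 + 25 nurses, 5 patients each, SD 12, target difference 6, ICC 0.1 (also 0.2), 20% loss, two-sided 5% (all Number of Participants). **Assumed, because not in the document:** baseline to 52-week correlation of 0.3, 0.5 and 0.7; trend in TAU; loss by arm.

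**1. The plan's own power.** With 4 analysed patients per nurse, the design effect is 1 + 3 × ICC.
- ICC 0.1: 1.3; effective n = 100/1.3 = 76.9 per arm; SE = 12 × √(2/76.9) = 1.93; power 87.3% (normal) or 86.0% (t, 48 df). Stated: 86%.
- ICC 0.2: 1.6; effective n = 62.5; power 79.8% or 78.2%. Stated: nearly 80%.

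The stated figures are reproduced.

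**2. Expected zero-change estimate.** With loss dH in HIP and dT in TAU (independent of outcome) and mean change *trend* in TAU:

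estimate = (1 − dH)(effect + trend) − (1 − dT) × trend

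| Loss HIP / TAU | Trend | True effect | Zero-change estimate |
|---|---|---|---|
| 20% / 20% | 0 | 6 | 0.8 × 6 = 4.8 |
| 30% / 10% | 0 | 6 | 0.7 × 6 = 4.2 |
| 10% / 30% | +5 | 6 | 0.9 × 11 − 0.7 × 5 = 6.4 |
| 30% / 10% | −5 | 0 | 0.7 × (−5) − 0.9 × (−5) = +1.0 |
| 30% / 10% | +5 | 0 | 0.7 × 5 − 0.9 × 5 = −1.0 |

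The bias can go either way.

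**3. Standard errors.** Simulation with 20% random loss in each arm, no trend, ICC 0.1, true difference 6, cluster-robust SE and 1,500 runs per setting. Mean SEs at correlation 0.3, 0.5, 0.7:

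| Scale | Observed data only | Zero change | Reduction |
|---|---|---|---|
| 52-week score | 1.92, 1.91, 1.92 | 1.73, 1.74, 1.76 | 8 to 10% |
| Baseline-adjusted | 1.83, 1.66, 1.36 | 1.53, 1.38, 1.13 | 16 to 17% |
| Change score | 2.26, 1.92, 1.48 | 1.82, 1.55, 1.20 | about 19% |

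The simulated zero-change estimates were 4.75 to 4.91. With nobody lost, the baseline-adjusted SEs would be 1.68, 1.53 and 1.26, so zero change reports smaller SEs than complete follow-up would give.

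**4. Lost patients who differ by arm.** Suppose there is no effect except that lost HIP patients fall by 6 points and lost TAU patients by 0. The all-patient difference is 0.2 × (−6) = −1.2. Zero change returns 0.0, because it gives both groups of lost patients a change of zero.

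**5. Selective loss.** With no true effect and HIP patients who declined preferentially lost, zero change replaces a fall with no change and so raises the HIP mean. In two simulated settings the baseline-adjusted zero-change estimate was a spurious 2.0 to 3.1 points. Its z value exceeded that of the observed-data analysis in both: 1.95 against 1.74, and 2.52 against 2.12. The size depends on how strong the selection is assumed to be.

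**6. What shifts by arm would show.** At 20% loss in each arm, adding δ to imputed scores gives effect = 6 + 0.2 × (δHIP − δTAU). With δHIP = −6 and δTAU = 0 this is 4.8, so in this setting zero change has the point estimate of one cell of such a grid. Using the SE of 1.93, the critical difference is 2.01 × 1.93 = 3.89. An estimate of 6 loses significance once lost HIP patients are (6 − 3.89)/0.2 ≈ 10.6 points worse, relative to TAU, than imputed.

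**The case against.** The strongest defence is that zero change is an openly named scenario and is valid on its own terms. When lost patients truly average zero change with individual scatter, so that the truth is 4.8, simulated coverage of the zero-change interval is 94.6 to 95.4%. Its SE also matches its sampling spread (for example 1.76 against 1.79). In the setting of step 3, coverage of the true 6 falls to 89 to 91% on the 52-week score and 81 to 88% after baseline adjustment, but that shortfall comes mainly from bias. The smaller SE is misleading only in so far as filled-in scores are read as observed ones. This part of the defence stands.

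Several stronger readings are tempting but unsupported:
- *The rule always shrinks the effect.* It does so under equal random loss without a trend. The 6.4 in step 2 is a counterexample.
- *The rule is blind to arm-dependent loss.* The estimate does respond to unequal loss rates (4.2 at 30%/10%). What it cannot do is vary the assumed outcome of lost patients by arm.
- *The missing versus non-missing comparison is pooled over arms.* The text states neither pooling nor splitting, and that detail can sit in the analysis plan, which is not shown.
- *A true effect will look fragile.* After baseline adjustment, the ratio of estimate to SE hardly moves in a simulation at correlation 0.7: 5.97/1.389 = 4.30 with observed data, 4.78/1.148 = 4.16 with zero change. The unadjusted analysis does lose power, from about 86% to 78%.

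It is also fair that multiple imputation is planned alongside, and that the wording leaves room for shifted versions of it. But zero change is a rule the article itself fixes, and standard multiple imputation under missing at random does not supply the missing test.

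**Conclusion.** The point holds as a limited one. Sensitivity analysis (i) fixes a single assumption for both arms and cannot be relied on as a conservative check. At the plan's SD, ICC and 20% loss, and with equal random loss and no TAU trend, it moves 6 to 4.8 with an SE 8 to 10% below the observed-data analysis, or 16 to 19% below when baseline is used as a covariate or through change scores. Under other loss patterns it can give 6.4 for a true 6, 1 point either way for a true 0, or a spurious effect with a larger z value than the observed-data analysis. The SE figures rest on assumed correlations of 0.3 to 0.7. The remaining figures rest on assumed trends and loss patterns that the document does not give.

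A reader might infer that the trial's main result is compromised. The documents do not support that: this is one of two sensitivity analyses, and neither the primary estimate nor the sample size uses it. It is an inexpensive improvement to a secondary analysis.

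**What to change.** Replace sensitivity analysis (i) with delta-adjusted multiple imputation, or keep zero change only as one labelled scenario beside it. Impute 52-week PCS from arm and baseline PCS with a nurse random intercept. Shift the imputed values separately in each arm over a range stated in advance, and report the shift at which the conclusion changes. The range should be wide enough to reach that point: in the illustration above it lies near 10.6 points, or 10.6/12 = 0.88 SD, so a range that stopped at the 6-point target difference would miss it.

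Cost: a sentence in the analysis section and a few hours of programming, with no new data. The downside is that a grid of results is reported in place of one number.
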